### *6.8.4 Lost to Follow-up*

---

A subject will be considered lost to follow-up if he/she does not appear for the scheduled study visit and study personnel are unable to contact the subject. Study personnel must make a reasonable effort to contact the subject and document the following contact attempts prior to declaring a subject to be lost to follow-up: three phone calls with at least 2 days in between each call followed by a certified letter. The first phone call must occur no less than 3 business days after subject has failed to show up for a visit.

### *6.8.5 Completed Subject*

---

A subject will be considered as having completed the study if he/she has completed all assessments through the 180-day visit. The 365-day visit will be used until the last subject completes the 180-day follow-up visit.

## *6.9 Study Site Discontinuation*

---

Study site participation may be discontinued if the Sponsor, the Investigator or the IRB/REB/ERC of the study site determines it necessary for medical, safety, regulatory or other reasons consistent with applicable laws, regulations and GCP.

## *6.10 Study Discontinuation*

---

The study will be discontinued if the Sponsor decides it necessary for medical, safety, regulatory or other reasons consistent with applicable laws, regulations and GCP. The study may be also discontinued if it reaches a futility conclusion during the interim analysis.

## 7 Statistical Analysis

---

Details of the statistical analysis, including the adaptive changes and handling of missing values will be described in the Statistical Analysis Plan (SAP), which will be provided as a separate document. This section provides key elements of the statistical approach.

### 7.1 Primary Efficacy Endpoint

---

The primary efficacy endpoint in this study is absolute difference in ISNCSCI Motor Score (ISNCSCIMS) between 180-day follow-up and baseline

$$\Delta\text{ISNCSCIMS}_{180-b} = \text{ISNCSCIMS}_{180 \text{ days}} - \text{ISNCSCIMS}_{\text{baseline}} \quad (1)$$

### 7.2 Secondary Efficacy Endpoints

---

- Change in ISNCSCI grade between baseline and 180 days
- SCIM at 180 days

### 7.3 Other Endpoints

---

- Change in ISNCSCI Sensory Score (Light Touch and Pin Prick) between 180 days and baseline
- Change in ISNCSCI Upper Extremity Motor Score between 180 days and baseline
- Change in ISNCSCI Lower Extremity Motor Score between 180 days and baseline
- Change in SF-36v2™ PCS, MCS and 8 dimensions between 180 days and pre-injury (recall)
- Change in EQ-5D health utility between 180 days and pre-injury (recall)
- GRASSP at 84 days and 180 days
- Change in pain NRS for at 14 days, 84 days, 180 days

### 7.4 Adverse Events

---

AEs will be recorded according to descriptions provided in Section 9.

### 7.5 Study Success

---

Study success is defined as follows:

Investigational treatment (riluzole) is superior to placebo. Study success is achieved if the one-sided null hypothesis of no superiority of riluzole group in  $\Delta\text{ISNCSCIMS}_{180-b}$  is rejected.

### 7.6 Statistical Testing of Primary Endpoint

---

The appropriate statistical approach is to test a single one-sided null-hypothesis that the difference between the investigational and the placebo arm is equal to or less than 0. Rejection of the null-hypothesis is consistent with superiority of the investigational treatment to the placebo.

$$H_0: \mu_I - \mu_C \leq 0$$

$$H_1: \mu_I - \mu_C > 0$$

Where:

$\mu_I$  and  $\mu_C$  are the means of the two independent normal distributions;

$\mu_I$  is the mean population value of the  $\Delta$ ISNCSCIMS180-b in the patients treated with riluzole;

$\mu_C$  is the mean population value of the  $\Delta$ ISNCSCIMS180-b in the patients treated with placebo.

The hypothesis will be tested by one-sided t-test at the alpha level of 0.025. If the test value exceeds the nominal critical point, the  $H_0$  will be rejected. If the test-value crosses the futility boundary, the  $H_0$  will be accepted.

### 7.7 Statistical Testing of Secondary Endpoints

Secondary endpoints will be tested for superiority. The statistical significance will be established by two-sided  $\alpha = 0.05$ .

### 7.8 Safety Evaluations

AEs will be classified by body system and preferred term. Relative frequencies of AEs will be compared between the riluzole and placebo arms using chi-square test with alpha = 0.05.

### 7.9 Sample Size Estimate

The required sample size is 316 evaluable subjects, or 158 subjects per study arm. The rationale for the sample size is as follows.

Sample size has been calculated to provide 90% power in testing the primary superiority hypothesis. The estimate has been calculated by PROC SEQDESIGN for SAS/STAT. Standard deviation for the primary outcome parameter has been made using the data from the STASCIS study (data on file with the Sponsor) (Table 3). This estimate is based on subjects with neurological level of injury from C4-C8 at arrival, the ISNCSCI Impairment grade “A,” “B” or “C” and time from injury to arrival of less than 12 hours.

**Table 3 Standard deviation estimate for the primary efficacy endpoint**

| Endpoint                            | Standard Deviation |
|-------------------------------------|--------------------|
| $\Delta$ ISNCSCIMS 180-b | 24.08              |

**Table 4 Sample size estimate  $\Delta$ ISNCSCIMS180-b**

| Plan ID                                           | Parameter            |
|---------------------------------------------------|----------------------|
| Type of the Hypothesis                            | 1-Sided              |
| Type I Error ( $\alpha$ )                         | 0.025                |
| Power (1 - $\beta$ )                              | 0.90                 |
| Randomization Ratio (Investigational vs. Control) | 1:1                  |
| Planned Number of Interim Looks                   | 2                    |
| Spacing of Looks                                  | 60%, 100%            |
| Hypothesis to be Rejected                         | H0 or H1 (binding)   |
| Boundary Family                                   | Published Function   |
| Boundary to Reject H0                             | Est. O'Brien-Fleming |
| Boundary to Reject H1                             | Gamma (-1)           |
| Difference of Means Assuming H 1       | 9                    |
| Standard Deviation ( $\sigma$ )                   | 24.08                |
| Sample Size                                       | 316 (158 per arm)    |

Under the above assumptions, the estimated sample size is 316 evaluable subjects (158 in the riluzole arm and 158 in the placebo arm). In order to account for loss of power due to loss of follow-up and possible adjustments for baseline factors we will increase sample size by 10% to **351 enrolled** subjects.

### *7.10 Justification for Effect Estimate*

There is no published minimally significant difference for ISNCSCIMS. The current effect estimate of 9 is arbitrarily set. This difference translates to 0.37 Cohen's d and is at the lower boundary of the moderate effect.

### *7.11 Statistical Performance and Simulations*

The statistical plan aims at efficient design that allows the demonstration of treatment efficacy while also allowing for early stop due to futility if the treatment does not appear to be successful.

Figure 2 shows rejection boundaries for H0 and H1 on the absolute delta scale for the interim and the final analysis.

**Figure 2 Rejection boundaries for ISNCSCI motor score**[figure not shown]

Table 5 shows the results of the statistical simulations of trial performance. Under the futility scenario (i.e. the difference in treatment effect between the placebo and riluzole equals zero), the trial has 81.8% probability to stop at the interim analysis and 2.5% probability to wrongly reject  $H_0$  at the final analysis. The 2.5% probability is consistent with chosen alpha level for the study. If the true effect is 50% of the anticipated effect (i.e. 4.5 points difference between the cohorts assuming no changes in the SD), the trial will have 62.9% power, before possible sample size adaptive adjustments. If the effect size is as expected, the trial will have 46.2% power at the interim and 90% power at the final analysis. Finally, if the effect is for 50% larger than anticipated (i.e. 13.5 points difference and the same SD), the trial will have 88.3% power at the interim and 99.8% at the final data look, before possible sample size adjustment.

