| Statistical Plan      | 
The statistical analysis will test the null hypothesis of the superiority of riluzole compared to placebo in change of ISNCSCI Motor Score between the baseline and the 180-day follow-up (<math>\Delta</math> ISNCSCIMS).
 
Statistical Test. The statistical testing of <math>H_0</math> for the primary endpoint will be organized as a 2-stage sequential adaptive design. There will be one interim analysis at about 60% of the accrued sample and the final analysis. The overall sequential design will be organized in the following way. The statistical design will address efficacy and futility. The statistical testing of <math>H_0</math> hypothesis will be performed as a one-way test with alpha level .025, testing the superiority of riluzole arm compared to placebo arm. The superiority of placebo over riluzole (i.e. harmful effect of riluzole) will not be tested as it has no clinical implication. Alpha-spending for the testing of <math>H_0</math> will resemble an O'Brien-Fleming distribution. The testing for futility (<math>H_1</math>) will consequently be organized as one-way testing. The beta spending for futility testing will follow <math>\gamma</math>-distribution with the parameter (-1). The results of the interim analysis will be reviewed by the DSMB and will not be shared with the sponsor, participating investigators or patients, except in the case that the study reaches stopping criteria.
 
Sample Size. Based on the above statistical design specifications and empirically-derived standard deviation for ISNCSCIMS change of 24.08 from a large case series of prospectively followed SCI subjects in an earlier study, a sample size of 316 subjects (158 in each arm) will have 90% power to detect 9 points difference in the <math>\Delta</math> ISNCSCI Motor Score at one-sided <math>\alpha = .025</math>. To account for losses to follow-up of up to 10%, the study will enroll 351 subjects.
 
The sample size estimate is based on certain assumptions. The main assumptions affecting the sample size is that of the true effect size and the standard deviation for the difference in the <math>\Delta</math> ISNCSCIMS. These assumptions will be verified during the study and sample size adjustment will be performed if needed, using the adaptive techniques. The sample size adjustment will be performed after the first interim analysis of the data, currently planned at about 60% of the data available at 180 days follow-up. The details of the adaptive design will be provided in a separate Statistical Analysis Plan (SAP).
 
Study success. Study will be considered to successfully confirm the working hypothesis if <math>H_0</math> for the primary endpoint has been rejected either at interim or the final analysis.
 
Secondary outcomes. Testing for all secondary outcomes will be based on appropriate statistical methods and two-way superiority testing. Secondary outcomes will not be tested at the interim analysis, except if
 |

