## *7.14 Randomization*

---

The randomization will be performed at 1:1 ratio between the investigational and control arms. Randomization will be carried out according to the blocks procedure. Block randomization is used to assign eligible subjects to the treatment arms in order to avoid serious imbalance in the number of subjects assigned to each group within a center. The pattern of the blocks will be concealed to avoid selection bias. Two block sizes will be used, with 2 and 4 subjects per block. Block sizes will be chosen at random. This scheme makes breaking the blinding by working out the block pattern extremely difficult and reasonably protects against biased allocation of subjects.

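### Protocol 7.11 gives 62.9% power for a 4.5-point effect, but that is Table 5's probability of accepting the null; the power is 37.1%

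*Protocol*

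**What the plan says.** The Protocol plans a two-look group sequential comparison of the change in ISNCSCI motor score from baseline to 180 days. Section 7.9 states: "Sample size has been calculated to provide 90% power in testing the primary superiority hypothesis". The assumed difference is 9 points, and section 7.10 says of it: "The current effect estimate of 9 is arbitrarily set".

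Section 7.11 then describes performance at true differences of 0, 4.5, 9 and 13.5 points and refers to Table 5. For half the anticipated effect, described as "4.5 points difference between the cohorts assuming no changes in the SD", it says that "the trial will have 62.9% power, before possible sample size adaptive adjustments".

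For 4.5 points Table 5 gives:

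- Reject Null: 0.08343 at the interim, 0.37114 by the final analysis.
- Accept Null: 0.35203 at the interim, 0.62886 by the final analysis.

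**The concern.** Power is the probability of rejecting the null when the stated effect is real. In Table 5 that is the Reject Null figure, 37.1%. The 62.9% in the text equals the Accept Null figure, which is the type II error.

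The error crosses the 50% line. A reader of the text learns that the trial would more likely than not detect half the anticipated effect, when it would more likely than not miss it. This is the only prose statement of how the trial performs under a real but smaller benefit. That scenario deserves attention, because section 7.10 gives no empirical basis for the 9 points and section 7.12 names the true effect size among the main assumptions to be verified during the study. The text also does not mention that, with a true 4.5-point benefit, the trial stops for futility at the interim about 35% of the time.

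**Working it through.** **1. Text against Table 5**

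| True difference | Text of 7.11 | Reject Null (interim; final) | Accept Null (interim; final) | Row used for power |
|---|---|---|---|---|
| 4.5 | 62.9% | 0.08343; 0.37114 | 0.35203; 0.62886 | Accept Null |
| 9 | 46.2%; 90% | 0.46172; 0.90000 | 0.04785; 0.10000 | Reject Null |
| 13.5 | 88.3%; 99.8% | 0.88301; 0.99761 | 0.00158; 0.00239 | Reject Null |

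The final column is cumulative: at 4.5 points, 0.37114 + 0.62886 = 1.00000. So 0.37114 is the overall power, not the power of the second stage alone. Only the 4.5-point figure comes from the Accept Null row.

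**2. Inputs for rebuilding the design**

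- One-sided alpha 0.025 (7.6 and Table 4: "The hypothesis will be tested by one-sided t-test at the alpha level of 0.025").
- Power 0.90 at a difference of 9, with 1:1 allocation (Table 4).
- SD 24.08 (Synopsis, Tables 3 and 4: "standard deviation for ISNCSCIMS change of 24.08").
- Looks at 60% and 100% of information, O'Brien-Fleming-type alpha spending, Gamma(-1) beta spending, binding futility (Table 4).

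**3. Boundaries and sample size**

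- Alpha spent at the interim: 2[1 − Φ(z(0.9875)/√0.6)] = 0.00381, so the interim efficacy bound is z = 2.669.
- Beta spent at the interim: 0.10 × (1 − e^0.6)/(1 − e^1) = 0.04785.
- Let θ be the mean of the final z statistic at a 9-point difference. The interim futility bound is then Φ⁻¹(0.04785) + θ√0.6. Solving jointly for total alpha 0.025 and power 0.90 gives θ = 3.321, a futility bound of 0.906 and a final critical value of 1.936.
- n per arm = 2(θ × SD/9)² = 2 × (3.321 × 24.08/9)² = 157.9, so N = 315.8. This reproduces the stated 316 (158 per arm).

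The rebuilt design reproduces the stopping probabilities in Table 5 at all four true differences to five decimals, and the expected stopping stages to three.

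**4. Power at 4.5 points**

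The mean of the final z is halved: 3.321/2 = 1.661. The mean of the interim z is 1.661 × √0.6 = 1.286.

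- Reject at the interim: 1 − Φ(2.669 − 1.286) = 0.08343.
- Accept at the interim: Φ(0.906 − 1.286) = 0.35203.
- Continue: 1 − 0.08343 − 0.35203 = 0.56454.
- Reject at the final analysis: the integral over z from 0.906 to 2.669 of φ(z − 1.286) × [1 − Φ((1.936 − √0.6·z − 0.4 × 1.661)/√0.4)] = 0.28771.
- Overall power: 0.08343 + 0.28771 = **0.37114**.
- Probability of accepting the null: 1 − 0.37114 = **0.62886**.

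A Monte Carlo run of two million trials gave 0.371.

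**5. Could another reading give 62.9%?**

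| Variant at 4.5 points | Power |
|---|---|
| Binding futility, as in Table 4 | 37.1% |
| Non-binding futility (N about 324) | 36.3% |
| Fixed design, 158 per arm, one-sided 0.025 | 38.2% |
| Fixed design, all 351 evaluable, one-sided 0.025 | 41.7% |
| Fixed design, 158 per arm, one-sided 0.05 | 50.6% |
| Fixed design, 158 per arm, one-sided 0.10 | 64.8% |

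Nothing at the Protocol's alpha comes near 62.9%. The last row is closest, but it uses an alpha that contradicts section 7.6. The planned design reaches 62.9% power only at a true difference of about 6.3 points.

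**The case against.** The strongest defence is that nothing operational rests on the sentence. The 316 evaluable and 351 enrolled subjects, the boundaries, the alpha, the interim timing and the 90% power at 9 points are all unchanged, and the correct probabilities stand in Table 5 directly after the text. On this view it is a mismatch between text and table in one section, not a flaw in design or analysis. That description is fair, and it limits the consequence. It does not make the printed power figure true.

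Three limits on the argument follow.

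- The case for a misread row rests on 9 and 13.5 points. At zero difference the text gives 81.8% as the probability of stopping at the interim. That is the Accept Null row (futility stops only); total stopping is 82.1%.
- The Protocol does not show that the DSMB or the sample size re-estimation uses the 4.5-point figure. Section 7.12 leaves the adaptive details to the SAP, and section 12.4 leaves DSMB operations to its charter. Any effect on them is an inference.
- The qualifier that the figure precedes any sample size adaptation offers no rescue, because Table 5 also describes the design before adaptation.

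**Conclusion.** The statement in section 7.11 is wrong. Power at a true difference of 4.5 points is 37.1%, not 62.9%, an overstatement of 62.9 − 37.1 = 25.8 percentage points. The probability of accepting the null is 62.9%, of which 35.2 percentage points arise at the interim.

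The result rests on the Protocol's own assumptions: SD 24.08, 316 evaluable subjects, looks at 60% and 100%, the Table 4 spending functions, binding futility and no sample size change. It needs no outside figure, since Table 5 already gives it and the rebuilt design confirms it. The error lies in the reported operating characteristic only. It should still be corrected, because it reverses the message about a smaller true effect.

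**What to change.** In section 7.11, replace the 62.9% power figure for the 4.5-point scenario with 37.1% power, and add that the probability of accepting the null is 62.9%, with 35.2 percentage points of it at the interim. Table 5 needs no change. If the 62.9% figure is repeated as power in any other trial document, correct it there too.

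The cost is one sentence in the Protocol and a less favourable stated figure. No patients are added, and the design and analysis do not change.

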**Table 5 Statistical simulation of trial performance**

| True Difference | Expected Stopping Stage | Source      | Stopping Probabilities |                |
|-----------------|-------------------------|-------------|------------------------|----------------|
|                 |                         |             | Interim Analysis       | Final Analysis |
| 0.0000   | 1.179                   | Reject Null | 0.00381                | 0.02500        |
| 0.0000   | 1.179                   | Accept Null | 0.81764                | 0.97500        |
| 0.0000   | 1.179                   | Total       | 0.82145                | 1.00000        |
| 4.5000   | 1.565                   | Reject Null | 0.08343                | 0.37114        |
| 4.5000   | 1.565                   | Accept Null | 0.35203                | 0.62886        |
| 4.5000   | 1.565                   | Total       | 0.43546                | 1.00000        |
| 9.0000   | 1.490                   | Reject Null | 0.46172                | 0.90000        |
| 9.0000   | 1.490                   | Accept Null | 0.04785                | 0.10000        |
| 9.0000   | 1.490                   | Total       | 0.50957                | 1.00000        |
| 13.5000  | 1.115                   | Reject Null | 0.88301                | 0.99761        |
| 13.5000  | 1.115                   | Accept Null | 0.00158                | 0.00239        |
| 13.5000  | 1.115                   | Total       | 0.88459                | 1.00000        |

### *7.12 Adaptive Design and Sample Size Re-estimate*

The current sample size estimate is based on numerous assumptions. The main assumption is that of the true effect size and the standard deviation for the  $\Delta$ ISNCSCIMS180-b. These assumptions will be verified during the study and sample size readjustment will be performed if needed, using the adaptive techniques. Other adaptive adjustments may occur at the same time. The adaptive adjustments will be performed after the first interim analysis of the data, currently planned at 60% data available at 180 days. The details of the adaptive changes will be described in a separate SAP.

### *7.13 Analysis Populations*

For definitions of subjects' status in the study see Section 6.8.

#### *7.13.1 Intention-to-Treat*

Consenting subjects who qualify, are randomized to a study arm and receive at least one dose of study medication (i.e. enrolled subjects) will be included in the Intent-To-Treat (ITT) analytic

sample primary analysis population, regardless of the actual treatment received. Screen failures will be recorded on the Screening SW and will not be included in the ITT group. Values for the subjects who do not have the 180 day end point will be imputed to create a complete ITT population.

### *7.13.2 Modified Intention-to-Treat*

---

The modified Intent-To-Treat (mITT) population is defined as all consenting subjects who receive at least one dose of study-directed treatment and have any follow-up. The mITT population will be used for safety analyses.

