## 6.7.2 Investigational Drug Dose and Administration

### 6.7.2.1 Dose

Subjects will receive a total of 28 doses of Investigational Drug, administered twice a day, for a total of 14 days. The riluzole group will receive riluzole in a dose of 100 mg at 0 hours and 12 hours (doses 1 and 2) followed by 50 mg doses every 12 hours for the next 13 days (doses 3 - 28). The control group will receive placebo capsules in a dose of two capsules at 0 hours and 12 hours (doses 1 and 2) followed by one capsule every 12 hours for the next 13 days (doses 3 to 28).

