### *6.7.6 Follow-up Evaluations*

---

Subjects will be evaluated according to the schedule set forth in this clinical Protocol. The schedule includes enrollment; surgery;  $72 \pm 12$  hours post-injury; 7 days  $\pm$  1 day after enrollment; 14 days  $\pm$  2 days; discharge from acute care; 84 days  $\pm$  14 days; 180 days  $\pm$  30 days; and 365 days  $\pm$  45 days. The study will continue until the last enrolled subject reaches the 180-day follow-up. As a consequence, a portion of subjects will not have 365-day follow-up visit.

All follow-up schedules are based on “Day 0” which for this study is the day of screening/enrollment visit, except for the visit 72 hours post-injury.

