#### *6.7.7.3 Surgery*

---

- Record operative data
- Check and record concomitant medications
- Obtain and record intra-operative complications
- Record immediate postoperative AE/SAE
- Obtain and record vital signs
- Check SWs for completeness
- Verify data and enter into eCRF preferably within 48 hours but no later than 14 calendar days from collection

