### *7.13.5 Primary Analysis Populations*

---

Primary efficacy analysis will be performed on the ITT population. Primary safety analysis will be performed on the mITT population.

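### The primary safety population requires an undefined post-dose follow-up, so some dosed subjects can drop out of the between-arm safety comparison

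*Protocol*

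**What the plan says.** Section 7.13.2 of the protocol defines the mITT set as "all consenting subjects who receive at least one dose of study-directed treatment and have any follow-up" and adds: "The mITT population will be used for safety analyses". Section 7.13.5 repeats the assignment: "Primary safety analysis will be performed on the mITT population". No safety set of all dosed subjects is defined.

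The intention-to-treat set in section 7.13.1, used for efficacy, also requires a dose ("receive at least one dose of study medication (i.e. enrolled subjects") but no follow-up; missing 180-day values are imputed.

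The safety test is in section 7.8: "Relative frequencies of AEs will be compared between the riluzole and placebo arms using chi-square test with alpha = 0.05". Section 6.2 names mortality and adverse events among the secondary objectives.

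**The concern.** A safety set normally depends on exposure alone. This one also depends on something that happens after exposure and that the outcome of interest can prevent. A subject who is dosed and then dies or leaves very early may not meet the condition, and then counts in neither the numerator nor the denominator of the only between-arm safety test the protocol states.

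Two features of this trial make the point more than formal.

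- The period at risk of exclusion contains the higher initial doses. Section 6.7.2.1 says: "The riluzole group will receive riluzole in a dose of 100 mg at 0 hours and 12 hours (doses 1 and 2".
- The synopsis (Statistical Plan) says that a harmful effect of riluzole will not be tested on the primary endpoint. A formal comparison for harm therefore rests on the safety analysis.

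**Working it through.** **1. When can a dosed subject be without follow-up?** Dose 1 is due no later than 12 hours after injury (section 6.7.1) and dose 2 follows 12 hours later (section 6.7.2.1), so both are due by 12 + 12 = 24 hours after injury. The first post-dose visit that applies to every subject is at 72 ± 12 hours post-injury (section 6.7.6, Table 1); its window opens at 72 − 12 = 60 hours. That leaves at least 60 − 24 = 36 hours after dose 2 in which only some subjects have a scheduled contact.

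**2. What could count as follow-up in that gap?**

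| Subject, before the 72-hour visit | Relevant text | In the mITT set? |
|---|---|---|
| Had surgery | 6.7.6: "The schedule includes enrollment; surgery"; 6.7.7.3: "Record immediate postoperative AE/SAE" | Probably, if surgery counts as follow-up |
| Withdrew while still on treatment | 6.8.3 requires a safety assessment no later than 30 days after the final dose taken | Probably, once assessed |
| Died, no surgery, death reported | 9.1.4 requires a serious adverse event report in 24 hours | Unclear; depends on the undefined term |
| No post-dose contact of any kind | None | No |

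The nearest definition, in section 7.13.3, ties 180-day follow-up to having an efficacy measurement at that visit. It does not say what counts for section 7.13.2.

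**3. How many subjects?** The base is the planned enrolment: 316 evaluable / 0.9 = 351.1, which agrees with the stated 351. The documents give no rate of dosed subjects without follow-up, so the rate below is an assumption:

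- 1%: 351 × 0.01 = 3.5, about 4
- 2%: 351 × 0.02 = 7.0, about 7
- 3%: 351 × 0.03 = 10.5, about 11
- 5%: 351 × 0.05 = 17.6, about 18

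**4. What could the exclusion do?** All counts here are assumed: 176 riluzole and 175 placebo subjects dosed, 9 later deaths in each arm, and e₁ and e₀ early deaths not counted as followed. The all-dosed rates are (e₁ + 9)/176 and (e₀ + 9)/175. The mITT rates are 9/(176 − e₁) and 9/(175 − e₀).

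| Early deaths, riluzole v placebo | All dosed | mITT |
|---|---|---|
| 2 v 2 | 11/176 = 6.25% v 11/175 = 6.3% | 9/174 = 5.2% v 9/173 = 5.2% |
| 4 v 2 | 13/176 = 7.4% v 11/175 = 6.3% | 9/172 = 5.2% v 9/173 = 5.2% |
| 10 v 2 | 19/176 = 10.8% v 11/175 = 6.3% (p = 0.13) | 9/166 = 5.4% v 9/173 = 5.2% (p = 0.93) |
| 2 v 10 | 11/176 = 6.25% v 19/175 = 10.9% | 9/174 = 5.2% v 9/165 = 5.5% |

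The p-values are from the uncorrected chi-square test. An early imbalance is flattened in whichever arm it falls; an equal number of early deaths changes the contrast hardly at all. The 10 v 2 row is deliberately extreme and is not a forecast.

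**The case against.** Much of the opposing case stands.

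- *Early events are observed.* Section 6.7.8 aims for decompression in the first 24 hours where feasible, so many subjects will have an adverse event record from surgery. Early withdrawals must be assessed for safety. Section 6.3.4 lists all adverse events, has the Safety Officer evaluate each serious one and has the safety board look at trends; section 12.4 gives the board the accumulating safety data. None of this is limited to the mITT set. A reader might infer that early deaths and drop-outs vanish from the trial. They do not; what is at risk is their place in the section 7.8 comparison. A listing does not replace that comparison.
- *Follow-up can be read generously.* Treatment starts in hospital, and a reported death could be taken as follow-up. That is a fair reading, but the text does not require it, and membership of the primary safety set should not be open to decision once events are known.
- *The direction is not fixed.* A reader might infer that the exclusion always hides harm from riluzole. It removes events from either arm, and more early deaths on placebo would mean a hidden benefit.
- *The efficacy set is not simply wider.* A reader might infer that every safety subject is also in the efficacy set. Section 7.13.1 additionally requires subjects to qualify. Sections 6.7.1 and 6.8.3 allow dosing before all screening laboratory results are back, so a subject could be in the safety set and outside the efficacy set.
- *No mortality was seen in the earlier study.* Section 5.2.6.1 reports none, in 36 patients (synopsis). But 0 of 36 has a one-sided 95% upper limit of 1 − 0.05^(1/36) = 8%, and section 5.2.6 shows that those patients received 50 mg at every dose.

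**Conclusion.** The point holds as a badly fixed population definition. It is not a detail left to the SAP, because the protocol itself sets the condition and names the set as primary for safety. Exclusion is certain only for dosed subjects with no post-dose contact. For subjects who die or leave before the 72-hour visit without surgery or a withdrawal assessment, it depends on a term the protocol does not define.

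The consequence is confined to the between-arm safety comparison, including any comparison of deaths made on that set. The primary efficacy test, the sample size and the alpha level are untouched. The size cannot be derived: 4 to 18 subjects rests on an assumed 1% to 5%, and any effect on the contrast rests on how early events split between the arms. If there were an early excess on riluzole, the rule as written would understate it.

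**What to change.** In section 7.13.2 remove the follow-up condition for safety, and in section 7.13.5 name the resulting set: every subject who received at least one dose of study medication, with every death and adverse event from dose 1 onward counted. Carry the same wording into the SAP before any unblinding.

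Merely defining follow-up so that a post-dose adverse event or death qualifies would be a weaker repair. A subject with an event would then enter because of the event, while an event-free subject without contact would stay out, so membership would depend on outcome.

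The cost is one sentence in each section and no new data: adverse events are already collected throughout the study (section 9) and serious ones reported in 24 hours (section 9.1.4). The change cannot recover events that nobody reported; such subjects would add only to the denominator. Grouping by treatment actually received is optional and is not needed to cure this defect.
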